### Sampling and recruitment

**
*Trial participants*
**. Women over 18 years old taking AET (tamoxifen, raloxifene, anastrozole, letrozole or exemestane) for early stage (I to IIIa) breast cancer, who have completed their last hospital treatment within the previous 12 months, are eligible to be part of the ROSETA pilot trial (
Table 5). All trial participants will be asked to complete the quantitative assessments of the process evaluation at baseline, 2 and 4-month follow-up alongside the pilot trial assessments.

**Table 5. T5:** Eligibility criteria for participation in the ROSETA pilot trial.

Inclusion Criteria	Exclusion Criteria
1. An informed consent form (signed and dated) 2. Capacity to provide informed consent 3. Women with early stage (1 to 3a) breast cancer according to the Tumour, Node, Metastasis (TNM) / American Joint Committee on Cancer (AJCC) staging system. *Note. Women being treated for a second primary breast cancer or a breast cancer local* * recurrence are eligible for the study, providing the most recent cancer is being treated with* * adjuvant endocrine therapy, and they meet all eligibility criteria. Women with bilateral breast* * cancer are permitted, providing at least one breast is affected by hormone receptor-positive* * disease.* 4. Aged ≥18 years old at time of screening for ROSETA’s pilot study 5. Have sufficient proficiency in English to be able to adhere to all intervention components and data collection required 6. Treated with curative intent 7. Completed their hospital-based treatment ( *e.g.*, surgery, radiotherapy and/or chemotherapy) for the current breast cancer within the last 12 months. *Note. Women are still eligible for the study if they are being treated with monoclonal* * antibody-based therapy such as trastuzumab, Kadcyla, pertuzumab, and Phesgo.* 8. Currently prescribed oral adjuvant Hormone Therapy (tamoxifen, raloxifene, anastrozole, letrozole, exemestane) 9. The participant is willing to complete the study questionnaires * 10. The participant is willing to be audio recorded during the therapy sessions * 11. The participant is willing and able to attend all ACT sessions either *via* video conference or telephone * 12. The participant is willing and able to complete home practice tasks * 13. Access to a mobile phone to receive SMS messages * 14. Willing to receive frequent SMS messages * 15. Access to a computer or smart device that can access the internet *	1. Stopped taking adjuvant hormone therapy if it is clinically contraindicated according to clinical recommendation 2. Women with Metastatic breast cancer 3. Currently or recently (last 6 months) involved in a similar research study where medication adherence is a primary outcome * 4. Currently attending psychotherapy/psycho-oncology/psychology/ counselling services, for any clinical reason * 5. Need for treatment for a severe mental health disorder or crisis, which is likely to interfere with participation ( *e.g.*, active psychosis, bipolar disorder, significant issues with addiction or self-harm or expressing active suicidal ideation with active plans and intent *) *Note, if concerned about the possible presence of risk of suicidal ideation* * with active plans and intent, then this can be assessed with the following* * questions, with patients ineligible if they answer ‘yes’ to 5c.* *Recently (in the last month):* * a. Have you had any thoughts about ending your life?* * b. (if yes) Have you thought about how you might go about it?* * c. (if yes) Do you intend to carry out this plan?* 6. Patients with a scheduled date for breast reconstruction surgery that is within their intervention delivery and follow-up period. *Note: Women* * planning to have a breast reconstruction but who have not scheduled a date* * for surgery are permitted.* 7. Auditory problems that would prevent the patient from participating in a telephone or video call, or hearing audio clips *

*Items marked with
* are collected via self-report*. Key:ROSETA= Refining and Optimising a behavioural intervention to Support Endocrine Therapy Adherence. SMS= Short Message Service. ACT= Acceptance and commitment therapy. This table has been reproduced with permission from Smith
*et al.*, (2023)
^
22
^.

Participation in the end of trial interview is optional. When providing initial consent at baseline, participants will be asked if they are willing to be contacted for an interview at the end of the trial. If willing, participants will be contacted with further information approximately three-months post-randomisation. Consent may be written or
*via* telephone. We aim to interview at least one participant from each experimental condition (corresponding to unique combinations of intervention components) in which they receive at least one component. Maximum variation purposive sampling will aim to achieve a mix of participants above and below 50 years old. Participants will be interviewed until we have gained sufficient information power for each study aim (fidelity, acceptability and trial experience)
^
42
^. Information power will be discussed in regular team meetings to inform further sampling. The specific aims of this study, high specificity of the sample and use of established theoretical frameworks to inform the interview indicates a smaller sample size may be appropriate. The interviewer (SG) has had experience interviewing women with breast cancer taking AET for similar purposes
^
43
^ and therefore a good quality of dialogue is expected
^
42
^. However, this will require ongoing evaluation as this is dependent on the interviewer and participants. The analytic strategy will explore themes across cases, rather than individual in depth analysis, which is likely to require an increase in sample size. Thus, a small to moderate sample size is expected to be required
^
42
^.

**
*Intervention deliverers (ACT therapists)*
**. Therapists delivering the ACT component will be Health and Care Professions Council (HCPC) or United Kingdom Council for Psychotherapy (UKCP) registered band 7a or above practitioner psychologists, or psychotherapists. Once the site has opened to recruitment, the therapist will be sent an invitation letter, information sheet and consent form. All consenting therapists delivering the ACT intervention component will be asked to complete the quantitative aspect (
*e.g.*, procedural fidelity checklists, fidelity assessments), and to participate in an end of trial interview.

One month before the end of the intervention delivery period, one therapist from each site will be randomly selected to be interviewed from those that have consented. Further therapists will be interviewed until the sample holds sufficient information power or there are no new consenting therapists left to interview. Information power will be discussed regularly in team meetings to inform further sampling
^
42
^. Based on the specific study aims, high specificity of the sample, use of theoretical frameworks, expected good quality dialogue and cross-case analysis, a small to moderate sample size is expected
^
42
^.

**
*Research nurses*
**. All RNs (or equivalent) involved in the recruitment of participants to the ROSETA pilot trial will be invited to participate in the process evaluation. Once the site has opened to recruitment, the RN will be sent an invitation letter, information sheet and consent form. If they consent, they will be asked to complete a questionnaire regarding the barriers and facilitators to recruitment at the end of the trial recruitment period.

### Assessment measures

**
*Participant*
**

Adherence to intervention components. To assess fidelity of receipt of the intervention components, participants will be asked two self-report items for each intervention component they were allocated to receive. The questions ask whether they received each intervention component, and how much of the intervention component they read. In relation to the ACT component, participants will be asked two additional items asking how much of the home practice tasks they completed, and how many of the audio files they listened to. Responses are on a 3-point scale; “none”, “at least some” and “all of”.

Acceptability Questionnaire (AQ)
^
41
^. The acceptability questionnaire, based on the TFA, will assess the acceptability of the individual intervention components, modified for each component
^
36,
41
^. Three items have been removed (ethicality, self-efficacy and opportunity costs) to reduce participant burden for those allocated to multiple intervention components. Five items remain assessing general acceptability, affective attitude, burden, perceived effectiveness and intervention coherence. Participants will answer on a 5-point Likert Scale.

For participants randomised to the ACT component, 15 extra items ask specifically about the acceptability of elements of ACT sessions and format. For participants randomised to the SMS component one additional item asks about the acceptability of the frequency of the SMS messages. One open question asks for any further comments about the acceptability of intervention components. The ‘general acceptability’ item from the AQ will assess the acceptability of participants’ experience in the trial as a whole. Participants will answer on a 5-point Likert Scale.

Study Participant Feedback Questionnaire (SPFQ)
^
44
^. The SPFQ will assess participants’ experience throughout the trial. This has been modified for the current trial. At baseline, participants will be asked two items about information received prior to the trial. Participants will answer on a 5-point Likert Scale. At the 2-month follow up, participants will be asked to complete three yes/no items regarding their experience during the trial. At the 4-month follow up participants will complete two items about their overall satisfaction with their experience in the trial, answering on a 5-point Likert Scale.

**
*Therapist*
**

ACT Fidelity Measure (ACT-FM)
^
40
^. ACT-FM is a measure of therapist fidelity to ACT principles when delivering treatment (
*i.e.*, competency). The ACT-FM therapist stance subscale will be used to assess fidelity of training and delivery of the ACT component. Only the therapist stance subscale will be used, as this is the subscale most relevant to therapist delivery of the ACT component. Four items assess ACT-consistent behaviours, and three items assess ACT-inconsistent behaviours. Each item is scored on a 4-point scale (0–3). Scores can range from 0–9 on each subscale. A score of >4 on ACT consistent behaviours, and <5 on ACT inconsistent behaviours will be considered competent.

Procedural Fidelity Checklist. A procedural fidelity checklist for each individual session will assess fidelity of delivery of the ACT component. The checklist is designed specifically for the ACT component in ROSETA, for therapists to self-rate whether they undertook core intervention procedures, such as reflection on the skills exercises and home practice tasks. It includes eight items for session 1 and 2, seven items for session 3, six items for session 4, and four items for session 5. A percentage score is calculated for each session by dividing the score achieved by the maximum score achievable in that session and multiplying by 100. Additional items ask therapists to record to what extent a participant has engaged with the module materials (participant manual, home practice tasks and associated audio files). In each checklist, the therapists will also record the number of times the session has been cancelled.

**
*Research Nurse*
**

Barriers and facilitators to recruitment. RNs will complete a questionnaire to report their experiences of recruiting to a factorial trial. Questions are based on the TDF
^
28
^ and cover knowledge of the trial design, the influence of resources, social pressures and emotional factors on recruitment, their motivation levels in recruiting to the trial, their decision processes when contacting a patient to schedule a recruitment appointment, and any procedural changes that would facilitate recruitment.

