### The ROSETA programme

The Refining and Optimising a behavioural intervention to Support Endocrine Therapy Adherence (ROSETA) programme aims to develop and optimise an intervention package to support adherence to AET in women with early-stage breast cancer. The ROSETA programme is guided by the Multiphase Optimisation Strategy (MOST), which is a framework used to optimise multicomponent behavioural interventions
^
17,
19,
20
^. MOST consists of three stages; (1) preparation, in which intervention components and a conceptual model detailing proposed mechanisms of action are developed, and any pilot testing is carried out, (2) optimisation, in which highly efficient experimental designs, such as factorial designs, are used to estimate the main effects and interaction effects of individual intervention components to build an optimal intervention package, and (3) evaluation, in which the optimised intervention package is compared with a comparator, typically using a parallel groups RCT
^
17,
19,
20
^. 

During the preparation phase of MOST, we combined the intervention mapping framework with MOST to develop four theory-based intervention components targeting distinct, unintentional and intentional barriers to AET adherence: (a) SMS messages to target forgetfulness; (b) information leaflet to target medication beliefs; (c) Acceptance and Commitment Therapy (ACT) guided self-help programme to increase psychological flexibility and reduce psychological distress; (d) side-effect self-management website to target AET side effects
^
21
^ (
Table 1). As part of this preparatory work, we developed a conceptual model for the intervention, detailing the mechanisms of action (
Figure 1). A full description of our approach to intervention development, along with detailed descriptions of the intervention components is available elsewhere
^
21
^.

**Table 1. T1:** Summary of intervention components in the ROSETA pilot trial.

Component	Target	Description	Theoretical basis
SMS	Forgetfulness/habit formation	SMS messages will be sent over 4 months providing practical strategies to support regular medication taking each day. The messages will be sent daily for 2 weeks, twice weekly for 8 weeks and weekly for 6 weeks.	Habit theory

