## Protocol

### Aims and objectives

This process evaluation has three aims: to assess (1) the fidelity of the intervention components; (2) the acceptability of the intervention components; (3) participant’s experience, and barriers and facilitators to recruitment and retention in a fractional factorial trial. These aims address the implementation and contextual factors themes outlined in the MRC framework
^
23
^. The specific objectives for each aim are:

1.Fidelity; Establish the fidelity of each intervention component across five domains of fidelity, guided by the NIHBCC fidelity framework
^
32
^:a.Design. To establish to what extent the intervention components target the behaviour change techniques (BCTs) they are intended to, and to what extent the components are distinct from one another;b.Training. To evaluate the adequacy of therapist training for the delivery of the intervention;c.Delivery. To assess if each intervention was delivered as planned;d.Receipt. To evaluate if participants receive and understand the intervention components they were allocated to;e.Enactment. To understand the degree to which participants implement the intervention components in their daily life;

Identify barriers to the fidelity of training, delivery, receipt and enactment of the intervention components, including any influential contextual factors.

2.Acceptability:a.Assess the acceptability of each intervention component3.Trial experience, recruitment and retention:a.Establish the barriers and facilitators to recruitment and retention of participants;b.Evaluate participant experience of trial participation.

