Fidelity of training (competency of delivery). The only intervention component to be delivered by healthcare professionals that requires training is the ACT component. Therapists will receive two half days of bespoke training from a clinical psychologist with expertise in ACT (CDG). To establish the adequacy of the training for delivery of the ACT component, a clinical psychologist (CDG) will assess the therapists recording of their first ACT session using the ACT Fidelity Measure (ACT-FM), which assesses therapist fidelity to ACT principles
^
40
^. The number of booster training sessions the therapists require will be monitored. Semi-structured interviews with the therapists will explore barriers to adequate training and scope for any improvements.

Fidelity of delivery. SMS receipt data will indicate whether a message has been successfully sent by the online system. The number of participants who opt-out of the SMS messages will be recorded. The number of information leaflets and website login details successfully sent to participants will be recorded by the site. For the ACT component, therapist scores on a procedural fidelity checklist will indicate which parts of the component were delivered (
*e.g.*, reflection on the utility, relevance and barriers to home practice tasks and introducing the following module). An expert ACT practitioner independent to the trial team will review 10% of all ACT session recordings using the ACT-FM, which assesses therapist fidelity to ACT principles. Reviewed recordings will include those conducted early and late in the trial and from all therapists involved.

Fidelity of receipt. Participants will be asked a single self-reported item to assess which intervention components they received. Self-reported engagement with the intervention component(s) will be collected, along with reasons for non-engagement. For the website, tracking data will be collected, including number of logins, time spent on website, pages visited and videos watched. Each participant will only be asked about the components they were randomised to receive. Semi-structured interviews will investigate fidelity of receipt and elicit any barriers or enablers to the receipt of all intervention components.

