### Data analysis plan

**
*Quantitative analysis*
**

Intervention fidelity. Descriptive statistics will summarise the quantitative intervention component fidelity assessments (
Table 2). For the ACT component, these will also be presented by site. Specific to the fidelity of design assessment, the first-order agreement coefficient statistic (AC1) will estimate the interrater reliability between the independent coders and the BCTs that the components intended to target
^
21,
39
^. Strength of fidelity of design will be defined in terms of pre-established AC1 thresholds; <0.2=poor, 0.2 ≤ 0.4=fairly poor, >0.4 ≤0.6=moderate, >0.6 ≤0.8=good, >0.8 and ≤ 1=very good
^
48
^. Discrepancies will be resolved through discussions between SG and the coders.

Intervention component acceptability. Descriptive statistics will be calculated for the individual items on the acceptability questionnaire, and overall, for each intervention component. Additional questions regarding the acceptability of specific aspects of the ACT and SMS components will be summarised. All summaries will be presented by component. Missing data will be summarised.

Barriers and facilitators to recruitment and retention of participants. Descriptive statistics will be presented for the RN barriers to recruitment and retention questionnaire, alongside qualitative data from the questionnaire. Summaries will be presented overall and by site. Missing data will be summarised.

Participant experience of trial participation. Descriptive statistics will be presented (1) for overall trial experience, and split by experience before starting the trial, during the trial and at the end of the trial; (2) for the one item of the AQ aimed at assessing general acceptability of the trial overall, by experimental condition and by site. Missing data will be summarised.

*

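### The self-report options for how much of a component was read or practised overlap as printed, so only none versus any is cleanly identified; this matters mainly for SMS and the leaflet

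*Protocol article*

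**What the plan says.** In the protocol article, under Assessment measures (Participant, Adherence to intervention components), each woman answers two items for every component she was allocated: "The questions ask whether they received each intervention component, and how much of the intervention component they read". Women allocated to ACT answer two more, on "how much of the home practice tasks they completed, and how many of the audio files they listened to". The response format is given once for these items: "Responses are on a 3-point scale; “none”, “at least some” and “all of".

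The items serve the receipt objective under Aims and objectives: "To evaluate if participants receive and understand the intervention components they were allocated to". The Data analysis plan treats them descriptively: "Descriptive statistics will summarise the quantitative intervention component fidelity assessments". Table 2 places them at 4 months.

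**The concern.** The items ask for an amount, but the upper two answers are not exclusive. Someone who has read all of a leaflet has also read at least some of it. Two women with identical behaviour can give different answers, and neither would be wrong. The reported share for *all of* then mixes how much was read with how the wording was understood. The middle option is also wide, running from a trace to nearly everything.

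Receipt is a named fidelity objective, and the Data analysis plan says the combined findings will be used to improve the components where needed. A leaflet that most women glanced at and one that most nearly finished could give the same table, yet they call for different action.

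**Working it through.** The documents state no figure for this measure, so there is nothing to reproduce. The check has three parts.

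**1. What the scale identifies.** Let *n*, *s* and *a* be the shares answering *none*, *at least some* and *all of*, with n + s + a = 1, and assume truthful answers.

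- Share with any receipt = s + a. This is exact, because the overlap affects only the upper two options.
- Share who received everything lies between a (no full reader chose the middle option) and a + s (everyone in the middle option was a full reader).
- Mean fraction received lies between just above a and a + s.

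The documents give no response shares. Purely as an assumed illustration, take n = 10%, s = 60%, a = 30%:

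- any receipt: 60% + 30% = 90%, exactly;
- received everything: from 30% to 30% + 60% = 90%;
- mean fraction received: from just over 30% to about 90%.

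The width of each range equals s: 20 points if s = 20%, 80 points if s = 80%. These are worst-case logical bounds and do not predict how women will answer.

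**2. Width of the middle option, taking SMS as the example.** Table 1 gives the schedule: "The messages will be sent daily for 2 weeks, twice weekly for 8 weeks and weekly for 6 weeks".

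- Messages: 7 × 2 = 14; 2 × 8 = 16; 1 × 6 = 6; total 14 + 16 + 6 = 36.
- Even if every woman takes the middle option to exclude *all of*, it covers 1 to 35 messages: 1/36 = 3% to 35/36 = 97%.

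**3. What else measures amount, by component** (Table 2; Design, Fidelity; Assessment measures, Therapist).

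| Component | Other quantitative records | Do they show amount received? |
|---|---|---|
| SMS | Messages successfully sent; opt-outs | No: sending and opting out, not reading |
| Leaflet | Number sent | No |
| Website | "tracking data will be collected, including number of logins, time spent on website, pages visited and videos watched" | Yes, usage |
| ACT | Sessions attended, cancelled or missed; therapist-recorded extent of engagement with manual, audio files and home practice; external rating of 10% of recordings | Yes, from other observers |

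Interviews cover receipt of all four components, but they are optional and the expected sample is small to moderate. They can explain how women used a component, but cannot give a distribution across everyone allocated to it.

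**The case against.** The strongest case against the point has four parts.

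- **The objective is worded as whether components are received and understood.** It does not ask for a graded dose, and none versus any answers its receipt part. This stands and limits the seriousness. The items themselves nevertheless ask how much and how many, so a reader will expect the upper two categories to mean something.
- **In an ordered list of three, many women would probably take the middle option to mean some but not all.** This is plausible, and it is why the bounds above should not be read as expected error. The documents offer nothing to confirm it, and removing the ambiguity needs only a few words.
- **Other data exist.** This is correct for the website and ACT. A reader might infer that the amount received cannot be told at all; the documents do not support that, because usage tracking, session counts and therapist-recorded engagement are planned for those two components. It does not help SMS or the leaflet.
- **The article condenses protocol version 3.0, and the questionnaire itself is not shown.** The printed form may word the options differently for each component. If it already makes them exclusive, the point reduces to correcting the article's description.

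A reader might also infer that the progression criterion on component adherence is compromised. That criterion is defined in a separate publication, so whether these items feed it, or whether *at least some* is a deliberate threshold there, cannot be checked.

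**Conclusion.** The point holds in a limited form and is minor. As printed, the response options are not mutually exclusive. None versus any is sound; the division between the upper two categories is not. The practical consequence falls mainly on SMS and the leaflet, where this item is the only quantitative measure of reading that the article describes.

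No size of misclassification can be derived. It would be tempting to state that the *all of* share is understated by some percentage, but any such figure would only return whatever proportion of full readers was assumed to choose the middle option. What can be said is that, with truthful answers, the overlap can move full readers only out of *all of*. The true share therefore lies between the observed *all of* share and the sum of the two upper shares.

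The conclusion assumes that the questionnaire carries the options as the article prints them.

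**What to change.** Reword the middle option to 'some, but not all' on the 4-month questionnaires still to be completed, and carry that wording into the optimisation trial. In the pilot report:

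- give none versus any as the figure comparable across both questionnaire wordings;
- give the *all* share separately by wording, with a caveat that the current wording allowed full readers to choose either upper option.

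Optionally, split the middle option into 'less than half' and 'half or more, but not all'. This would grade partial receipt for SMS and the leaflet, and combining the upper three options recovers any receipt. It is partly a matter of preference: recalling at 4 months whether more than half of 36 messages were read may not be accurate.

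The cost is a small amendment to response wording, with no added items. The downside is that responses on the current wording are fully comparable with later ones only after collapsing to none versus any. Recruitment was open when the article was submitted; if all 4-month questionnaires have since been returned, what remains is the reporting caveat and the corrected wording for the optimisation trial.
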